## Abstract

**Background:**

The encouragement of healthy lifestyles for obesity prevention in young people is a public health priority. The European Youth Tackling Obesity (EYTO) project is a multicentric intervention project with participation from the United Kingdom, Portugal, the Czech Republic and Spain. The general aim of the EYTO project is to improve lifestyles, including nutritional habits and physical activity practice, and to prevent obesity in socioeconomically disadvantaged and vulnerable adolescents. The EYTO project works through a peer-led social marketing intervention that is designed and implemented by the adolescents of each participating country. Each country involved in the project acts independently. This paper describes the “Som la Pera” intervention Spanish study that is part of the EYTO project.

**Methods/Design:**

In Spain, the research team performed a cluster randomised controlled intervention over 2 academic years (2013–2015) in which 2 high-schools were designated as the control group and 2 high-schools were designated as the intervention group, with a minimum of 121 schoolchildren per group.

From the intervention group, 5 adolescents with leadership characteristics, called “Adolescent Challenge Creators” (ACCs), were recruited. These 5 ACCs received an initial 4 h training session about social marketing principles and healthy lifestyle theory, followed by 24 sessions (1.30 h/session) divided in two academic years to design and implement activities presented as challenges to encourage healthy lifestyles among their peers, the approximately 180–200 high-school students in the intervention group. During the design of the intervention, it was essential that the ACCs used the 8 social marketing criteria (customer orientation, behaviour, theory, insight, exchange, competition, segmentation and methods mix). The expected primary outcomes from the Spanish intervention will be as follows: increases in the consumption of fruits and vegetables and physical activity practice along with reductions in TV/computer/game console use. The secondary outcomes will be as follows: increased breakfast consumption, engagement with local recreation and reduced obesity prevalence. The outcomes will be measured by the Health Behaviour in School-aged Children Study (HBSC) survey at baseline and at the end of the intervention.

In the control group, no intervention was implemented, but the outcome measurements were collected in parallel with the intervention group.

**Discussion:**

This study described a new methodology to improve lifestyles and to address adolescent obesity.

**Trial registration:**

ClinicalTrials.gov: NCT02157402. Registered 03 June 2014.

**Electronic supplementary material:**

The online version of this article (doi:10.1186/s12889-015-1920-1) contains supplementary material, which is available to authorized users.

## Background

Obesity is an important global public health problem, and its long-term consequences are well documented [1–3]. The prevalence of excess weight and obesity in childhood is increasing in different countries. In Europe, the prevalence of excess weight, including overweight and obesity, is 19–49 % in boys and 18–43 % in girls, whereas the obesity prevalence is 6–26.6 % in boys and 5–17 % in girls [4]. In developed countries, obesity is also related to socioeconomic status: obesity rates follow a social gradient in which the highest rates are present in racial/ethnic minorities and socioeconomically disadvantaged populations [5, 6].

Once obesity is established, it is difficult to treat, highlighting the urgent need for successful strategies and policies to revert trends in weight gain, sedentary lifestyles and inadequate nutritional habits, especially in vulnerable youth populations [6–8].

The improvement of healthy lifestyles through modification of eating habits, daily physical activity practice and avoiding sedentary behaviour are the principle modifications that can prevent or reduce the risk of obesity [9]. Specific recommendations based on expert opinion or supported by clinical studies are proposed [10]. These recommendations are the periodic surveillance of obesity status of children and adults, education of children and families about healthy lifestyles, community enrolment in health advice and health education, assure a balanced nutrition and breastfeeding in early infancy and perinatal period, school-based interventions on health education focused on healthy eating and physical activity, home-based interventions, and support of health authority and registration. The authorities should contribute in encouraging people in disadvantaged areas to eat healthier by improving the availability, quality and pricing of healthy food in these localities [11] and encouraging them to perform more physical activity by providing access to sport grounds and green spaces [12].

Nutrition and healthy lifestyle education for adolescents have to be planned differently than for other educational ages because the cognitive and social developmental processes, such as the shifts towards abstract thinking and problem-solving skills, questioning adult authority, increased autonomy from parents, and an increased reliance on peers as a source of identity, support, and normative behaviour, develop during this life period [13–20]. This age period presents both a challenge and an opportunity to offer new learning and teaching strategies to engage adolescents and motivate them to make healthy food choices [13, 14]. The influence of peers on young people’s health behaviours is acknowledged [16–19], and interventions using a peer-led model for health promotion have shown positive effects [20].

Social marketing when it is conscientiously applied, has been identified as a possible strategy to change behaviours [21]. Kotler and Zaltman expressly defined social marketing in 1971 as “a social influence technology involving the design, implementation and control of programs aimed at increasing the acceptability of a social idea or practice in one or more groups of target adopters” [22]. This term was re-described by Andreasen in 1994 as “the application of commercial marketing technologies to the analysis, planning, execution and evaluation of programs designed to influence the voluntary behaviour of target audiences in order to improve their personal welfare and that of their society” [23].

Doctrines and tactics from commercial marketing for social change programs can improve the strategic value of health communication and increase the likelihood that people will make healthy behavioural choices [22–25].

To help strengthen the use of effective social marketing approaches, the Social Marketing National Benchmark Criteria (SMBC) was developed by the National Social Marketing Centre (NSMC) in the United Kingdom [26]. The purpose of this benchmark is to create support for a better understanding of social marketing that takes into account the 8 basic SMBC principles: customer or participant orientation, behaviour, theory, insight, exchange, competition, segmentation and methods mix, as well as the promotion of a consistent approach to review and evaluate projects [26].

Some studies suggest that the use of social marketing strategies to modify behaviour, lifestyles and other aspects of diet and physical activity through an intervention (target audience played an active role) or a campaign (target audience played a passive role) can reduce the overweight or obesity prevalence among children and adolescents. There are some social marketing campaigns that demonstrate positive attitude and behaviour effects in children, such as the VERB social marketing campaign to increase physical activity among youth [27], Canada’s ParticipACTION national physical activity mass media campaign targeting parents of elementary school-aged children [28] and an intervention focused on improving the snacking habits of pre-school children [29]. By contrast, “The 5,4,3,2,1 go! Intervention” [30] demonstrated effects on parental behaviour and did not affect children [31]. The Change4Life campaign, a national social marketing program implemented in the United Kingdom to reduce obesity [32], demonstrated positive effects on awareness but little impact on attitudes and behaviours. However, the effectiveness of these campaigns requires further research on behaviour modification using randomised, controlled intervention studies to determine the appropriate number of criteria and the key social marketing criteria that will have the greatest impact on achieving the intervention objectives.

The European Youth Tackling Obesity (EYTO) project looks to contribute the description and evaluation of interventions to tackle obesity in adolescents by recruiting young people to design and implement peer-led social marketing interventions that promote healthy eating and physical activity among young people aged 13–16 years with low income who are vulnerable to obesity. The general aims of the EYTO project are to improve lifestyles, such as nutritional habits and physical activity practice, and to prevent obesity in socioeconomically disadvantaged and vulnerable adolescents. The secondary aims are to reduce the modifiable causes of obesity amongst disadvantaged young people; to improve health, education and social outcomes for young people who are obese; to contribute to a reduction in health inequalities among young people; and to increase the participation of young people in the development of interventions to address obesity.

This paper describes the “Som la Pera” Spanish intervention study design of the EYTO project, which proposed performing a school cluster randomised controlled trial.

## Methods

### European study design

This is a multicentric peer leadership intervention involving the participation of the United Kingdom, Spain, Portugal and the Czech Republic. Five selected adolescents (in each country) are tasked with designing and implementing a social marketing intervention, using the SMBC as a basis for the design, for 180–200 schoolmates. The selection of 5 ACCs per country was done as an easy and rapid way to design and prepare the challenges. The intervention should encourage healthy lifestyles among their peers of the same age in disadvantaged neighbourhoods; the adolescent peer-led model is more effective at achieving positive results in health behaviour than the adult-led models applied in school-based studies [33]. Adolescent peer-led interventions use the youth empowerment theory based on engaging young people in the decision-making process to improve their health and well-being [34]. Because the EYTO is a multicentric project in which each country acts autonomously and because the design and implementation of the interventions are directed by different adolescents in the participating countries, this protocol only reports the description of the Spanish study design.

The procedures and progress reports of work deliverables will be led by the Spanish management team according to the schedule’s National Children’s Bureau (NCB) to the European Commission, with a frequency of 6 months.

The communication of the results to the participants, healthcare professionals, and the public will be performed via publication, reporting in a results database, and other data-sharing arrangements. Authorship eligibility is in accordance with the best practices and ethical guidelines. If necessary, we will guarantee public access to the full protocol, participant database and statistical code.

### Spanish study design

The “Som la Pera” intervention is a school cluster randomised controlled trial. The participating Spanish city was Reus (Catalonia). Local authorities have already identified public high-schools that they agree serve low-income neighbourhoods that are considered disadvantaged areas. From the 9 public high-schools identified in these neighbourhoods, 4 high-schools were randomly selected. The randomisation code was computer generated. The high-schools were assigned to the control or intervention arm at a ratio of 1:1 via an interactive electronic response system hosted by the Nutrition and Health Technology Centre (CTNS) in Reus, Spain. The unit responsible for the randomisation took no further part in the study. Because the researchers know the names of the four high-schools, allocation concealment was not performed. The project consists of five main phases, as shown in Fig. 1. The first phase included the randomisation and allocation of the high-schools in the disadvantaged area into the two intervention and two control high-schools. High-school teachers from the randomised intervention group selected the five adolescents according to their knowledge of the students by considering leadership characteristics and English level (because the students will participate in EYTO European meetings), 2 adolescents from one high-school and 3 from the other high-school. These 5 adolescents will be referred to in this protocol as the Adolescent Challenge Creators (ACCs). The study characteristics are summarised in Table 1.

**Fig. 1 Fig1:**
[figure not shown]
Spanish Intervention Schedule of the European Youth Tackling Obesity (EYTO) Project

**Table 1 Tab1:** General study characteristics

Arm	High school information	Assigned interventions	Population	Primary and secondary outcomes
Intervention group	High-school A	The intervention group will receive an intervention consisting of challenges designed by 5 ACCs. These activities must have social marketing criteria.	High-school A	Primary outcome: consumption of fruits and vegetables, physical activity practice, and TV/computer/game console use. Secondary outcomes: breakfast consumption, engagement with local recreation and obesity prevalence
The intervention group received challenges designed by ACCs that promote healthy lifestyles.	Economically disadvantaged		Students from high schools from low-income neighbourhoods, who are 13 to 16 years of age:	
	Size: 3 classes/level		a) 3 to 5 ACCs	
	Public		b) 80-100 adolescents	
	Reus			
	High-school B		High-school B	
	Economically disadvantaged		Students from high schools from low-income neighbourhoods, 2who are 13 to 16 years of age:	
	Size: 4 classes/level		a) 2 to 5 ACCs	
	Public		b) 80-100 adolescents	
	Reus			
Control group	High-school A	No intervention is assigned for this group.	High-school A	The same outcomes were measured with the same tools and over the same time frame as in the intervention group.
The control group no received challenges to promote healthy lifestyles.	Economically disadvantaged		Students from high schools from low-income neighbourhoods, who are 13 to 16 years of age:	
	Size: 3 classes/level		b) 80-100 adolescents	
	Public			
	Reus			
	High-school B		High-school B	
	Economically disadvantaged		Students from high schools from low-income neighbourhoods, who are 13 to 16 years of age:	
	Size: 4 classes/level		b) 80-100 adolescents	
	Public			
	Reus			

### Participants and professional experts

The inclusion criteria were as follows: participants were between 13 and 16 years of age, attended one of the four randomised high-schools and had an informed consent signed by their parents or legal guardians. In addition, the five ACCs selected in the intervention group were included if they fulfilled the inclusion criteria mentioned previously, displayed leadership characteristics, had at least a working knowledge of the English language (for the International EYTO meetings) and were highly motivated and committed to the study. The lack of any inclusion criteria was the first and only exclusion criterion.

The professional experts who participate in “Som la Pera” intervention are:Physicians: physicians specialist on health education and promotion led the implementation of the study from the recruitment process to the end of the experimental protocol by meetings with stakeholders like high-schools’ director or local policy-makers and health and educators administrators. They were in charge of designing, performing and revising the evaluation process throughout the study.Nutritionists: nutritionists with expertise on health education and health promotion led the high-school recruitment process by meetings with parents and adolescents explaining the project, recollected the informed consent of parents and adolescent to participate in the study and, coordinated the logistical issues of the study. They contributed to support the evaluation of primary and secondary outcomes through the validated questionnaire in high-schools computer classrooms to solve adolescents’ questions of lifestyles and behaviour evaluation questionnaire. The nutritionists were responsible for the dietary and healthy lifestyle training of the 5 ACCs.Managers: The managers coordinated the Spanish intervention among the participating countries. They supervised all of the scientific work, from the intervention trial design to the scientific data interpretation.Publicists and Journalists: publicists and journalists experts on health communication were responsible for the communication training of the 5 ACCs. Even though the 5 ACCs were in charge of the communication and dissemination campaign (lifestyles messages and intervention challenges), publicists and journalists are in charge to disseminate the general information of this intervention and European project to general population through local, national and international newspapers and television media.

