#### Additional information

This study followed the SPIRIT [37] and TIDieR protocol description recommendations [38] as presented in Additional file 1 and Additional file 2. The participation, schedule of enrolment, interventions and assessment are presented in Table 4. Finally, a cluster CONSORT checklist and flow diagram were used to summarise the description of study when the study and analysis were completed [39].

**Table 4 Tab4:** Spanish EYTO participation, schedule of enrolment, interventions and assessment

	Study period							
	Enrolment	Allocation	Post-allocation					
	Phase 1				Phase 2			Phase 3
Timepoint	-t_1_	a0	t_1_	t_2_	t_3_	t_4_	t_5_	t_6_
	May 2014_(after CEIC approval)_	May 2014	May 2014	May 2014	May 2014	September 2014	September 2014	October 2014
	High-Schools of low income in Reus are included in this phase.	4 high-school are randomly chosen, 2 in the intervention and 2 in the control group	Control High-school meeting, Separate Intervention high-school meeting and 5 ACC selection	Social marketing, health promotion and communication training for 5 ACCs	Each participant answered the HBSC Survey.	Implementation of challenges by the 5 ACCs with help of stakeholders for their peers.	Preparation of the ACC presentation of the first academic Spanish intervention at the EYTO meeting in London.	Meeting of 5 ACCs from the 4 EYTO participating countries in London to pool designed activities and exchange ideas. Successful intervention activities can be re-implemented.
	Randomisation is performed.			Design of the intervention. Information and informed consent signed	Implementation of interventions by the 5 ACCs for their peers in high-school for 12 weeks.			
Enrolment:	360–400 adolescents from low-income neighbourhoods.							
Eligibility screen	X		X					
Informed consent								
[List other procedures]								
Allocation	180–200 from intervention group and 180–200 from control group							
Intervention			Training of 5 ACCs to design activities		HBSC Survey Implementation of activities during 12-week period	Implementation of social event challenges in the community and local markets for their peers		Evaluate the activities performed during 12-week period (1^st^ academic year)
Control			This group did not receive any interventions		HBSC Survey			
Assessments: List baseline variables	X	X	X				X	X

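### The nutritionists who train the peer leaders also answer pupils' questions during the self-reported outcome survey, which risks a reporting shift of unknown size that differs by arm

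*Protocol article*

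**What the plan says.** Under Participants and professional experts, the protocol article lists the nutritionists among the staff who take part in the intervention ("The professional experts who participate in “Som la Pera” intervention are" introduces the list) and gives them three tasks that bear on this point.

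- Recruitment: they "led the high-school recruitment process by meetings with parents and adolescents explaining the project", and they collected consent.
- Training: "The nutritionists were responsible for the dietary and healthy lifestyle training of the 5 ACCs".
- Outcome collection: "They contributed to support the evaluation of primary and secondary outcomes through the validated questionnaire in high-schools computer classrooms", with the stated purpose "to solve adolescents’ questions of lifestyles and behaviour evaluation questionnaire".

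Table 1 gives the primary endpoints: "Primary outcome: consumption of fruits and vegetables, physical activity practice, and TV/computer/game console use". Table 3 shows that each is a questionnaire item answered by the pupil. Body mass index, a secondary outcome, also rests on weight and height as the pupil reports them. Table 4 says of the baseline time point "Each participant answered the HBSC Survey" and schedules the survey again in February 2015, in both arms.

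On knowledge of the arm, Spanish study design states: "Because the researchers know the names of the four high-schools, allocation concealment was not performed".

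**The concern.** Self-reported diet, activity and screen time are open to the influence of who is in the room and how a question is explained. Several Table 3 items need interpretation by the pupil: what counts as fruit or vegetables, as an active hour, or as a breakfast. The article gives the job of resolving such doubts to the professional group that taught the ACCs the content of the campaign. These staff can be expected to know the arm, because the ACCs they train come only from intervention schools.

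At baseline the campaign had not reached the pupils. At the end survey it had reached one arm only. A reporting shift that arises then is not balanced by randomisation, and adjusting for baseline answers does not remove it. Because every primary outcome is self-reported, none of them provides an objective check on the others. At stake is whether a modest between-arm difference at the end survey reflects behaviour or reporting.

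**Working it through.** The article gives no figure for this effect, so there is nothing to reproduce directly. The check has two parts: whether the role overlap is really stated, and what a shift of a given size would do.

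**1. The texts side by side**

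| Element | Where (protocol article) | What it establishes |
|---|---|---|
| Nutritionists train the ACCs in diet and lifestyle | Participants and professional experts | Link to the content of the intervention |
| Nutritionists answer questions at the survey | Same paragraph | Link to outcome measurement |
| Primary outcomes are HBSC questionnaire items | Tables 1 and 3 | Self-report throughout |
| Researchers know the schools | Spanish study design | Allocation known to the team |
| Same outcomes, tools and time frame for controls | Table 1 | Survey help is not described as limited to one arm |

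The overlap is therefore a stated choice and not a detail left out of a condensed article. What is not stated is that help differed between arms.

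**2. Size of a hypothetical shift**

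Target difference, from Statistical analysis plan: 0.5 portion. The fruit and vegetable item in Table 3 records frequency, so an occasion is treated here as a portion.

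Assumptions, none taken from the documents: a share p of intervention pupils moves up one category at the end survey, with p = 0.10 to 0.25, and no control pupil does. Spurious difference = p × step.

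- Large step, once a day to more than once a day, taken as about 1 occasion a day: 0.10 × 1 = 0.10 and 0.25 × 1 = 0.25. Divided by 0.5: 20 % and 50 %.
- Smaller step, 2–4 days to 5–6 days a week, using midpoints: (5.5 − 3)/7 = 2.5/7 = 0.36 occasions a day. Then 0.10 × 0.357 = 0.036 and 0.25 × 0.357 = 0.089. Divided by 0.5: 7 % and 18 %.
- Equal shift in both arms: p × step − p × step = 0.

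The combined range is about 0.04 to 0.25 occasions a day, or 7 to 50 % of the target. The 7 % is not a floor, since some steps lower on the scale are smaller still.

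**3. What such a shift would do to the test**

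The article gives no standard deviation. Solving backwards from 121 per group, 90 % power, two-sided 5 % and a difference of 0.5: SD = 0.5 / [(1.960 + 1.282) × √(2/121)] = 1.20. With SD 1.2 the same formula returns 122 per group against the stated 121. This shows only that the SD was solved consistently; it does not reproduce the plan independently.

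Standard error = 1.2 × √(2/121) = 0.154, ignoring clustering. With no true effect and a shift b in the intervention arm only, the two-sided rejection rate is Φ(b/0.154 − 1.96) + Φ(−b/0.154 − 1.96):

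| Shift b (portions) | Rejection rate at nominal 5 % |
|---|---|
| 0.05 | about 6 % |
| 0.10 | about 10 % |
| 0.25 | about 37 % |

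Clustering would enlarge the standard error, so the same shift would raise the rejection rate less in an analysis that allows for it.

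**The case against.** The strongest reply is that the same staff and the same tools served both arms. Table 1 says controls were measured with the same tools over the same time frame, and nothing restricts survey help to intervention schools. An effect of mere presence that is equal across arms cancels. This stands for presence as such. It does not fully cover unscripted clarification by people who know the arm, or the possibility that exposed pupils respond differently to the same staff.

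Second, the nutritionists train five ACCs, and it is the ACCs who design and run the challenges. The nutritionists' documented wider contact with pupils is recruitment and consent, which took place in both arms. A reader might infer that the survey was supervised by staff who delivered the campaign to the pupils. The article does not say so. The Intervention section also attributes the training sessions to a university specialist. That may be the same people, but the overlap is established for a professional group and not for named individuals.

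Third, intervention pupils may over-report because they have heard the campaign, whoever supervises. That stands. It is inherent in unblinded self-report, and changing supervisors does not remove it.

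Fourth, the statement on allocation concealment concerns assignment, not blinding at measurement. It supports only the point that the team knew the arms. Pupils appear to enter their own answers on computers, so staff do not record them.

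**Conclusion.** The concern holds as a risk. The article gives one professional group both the ACCs' lifestyle training and the clarification of self-reported outcomes, with allocation known to the team. This could produce a reporting shift that differs by arm at the end survey.

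Two stronger readings are tempting and unsupported. One is that the arrangement actually biases all three primary outcomes in favour of the intervention. The documents show neither that a differential shift occurred nor its direction, and an equal shift would cancel. The other is that the effect amounts to 20 to 50 % of the target difference. That figure uses only the largest response step, an unsourced share of pupils and no shift among controls.

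The illustrative range of 7 to 50 % rests on an assumed 10 to 25 % of intervention pupils moving one category, none of the controls moving, and an occasion counting as a portion. It shows that a modest shift would matter against a 0.5-portion target; it is not an estimate. Nothing comparable was calculated for physical activity or screen time. The point is worth acting on mainly because the remedy costs little.

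**What to change.** Put the answers to predictable questions into one fixed on-screen help text, used in all four schools at both time points. Supervisors may read it out but not interpret it. Have the same small team of existing project staff, with no part in ACC training, supervise the survey in every school.

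Using different teachers in each school would be a poorer choice. It would tie supervisor to school, with only two schools per arm, and teachers in intervention schools know the arm too. A common team may also know the arm, so the fixed text matters as much as the change of staff.

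The cost is some rescheduling of staff and a short help text, with no added visits or measurements. The downside is that pupils get less expert clarification.

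Table 4 places the surveys in May 2014 and February 2015, and the article describes the measurements in the past tense, so this may come too late. In that case, report for each school and time point who attended and what help was given, and limit the conclusions on the self-reported outcomes accordingly.
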